### Data management {19}

Participants IDs will be used for confidentiality purposes and these IDs will be linked to demographic information securely and separately. The final data set of RCT will have coded data and can only be assessed by principal investigators. Data coding will be done by allocating medical record numbers. Data entry will be done electronically once paper-based case report form (CRF) has been received at the trial office. Once the data is entered, CRF will be destroyed to ensure safety and security. Data collection from the site and data entry into the database will be done by a different set of trained site investigators. All outcomes will be double-checked by the researchers prior to data collection and data storage. To ensure data’s integrity and safety, various meetings by the research team will be conducted on a regular basis.

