### Outcomes {12}

Primary outcomes will include time to SARS-CoV-2 RT-PCR clearance, alleviation of symptoms, and better high-resolution computerized tomography (HRCT) chest score. Thirty-day mortality will be used as a secondary outcome. SARS-CoV-2 RT-PCR will be done on admission day (0 day) and then after every 4th day for 12 days or till the symptoms are resolved and RT-PCR gets negative. Symptom resolution is defined by the resumption of mild to moderate symptoms COVID-19 symptoms (defined by the definition of symptoms). RT-PCR will only be shown as positive or negative (as a limitation of our study of not getting the viral load). Time taken for the alleviation of symptoms will be measured as the number of days the patient remained symptomatic, i.e., the difference between onset of COVID-19 symptoms to complete resolution. HRCT chest scoring will be done as follows: Lungs divided into five lobes and each lobe is scored as 0 (no involvement), 1 (< 5% involvement), 2 (up to 25% involvement), 3 (26–49% involvement), 4 (50–75% involvement), and 5 (> 75% involvement). The overall HRCT chest score will be from 0 (no involvement) to 25 (maximum involvement) [16]. The HRCT findings are described via standard international terms, which are classified by the Fleischner Society glossary with peer-reviewed literature on viral pneumonia. The terms being used are ground glass opacity (GGO), crazy-paving pattern, and consolidation [17, 18]. Like a previous study [19], a maximum of 4 HRCT chest will be performed starting from day 0 followed by every fourth day till patients’ PCR become negative.

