## Data collection and management

### Plans for assessment and collection of outcomes {18a}

Microsoft Access, a database management system (DBMS) of Microsoft Office, will be used to ensure the data safety. SARS-CoV-2 RT-PCR test and HRCT score will be done every fourth day while COVID-19 symptoms evaluation will be done on daily basis to access the time taken for the alleviation of symptoms. Thirty-day mortality will be assessed by the number of deaths per group after 30 days of randomization in all groups. All trial data will be collected by site investigators and two site investigators will enter the data, recheck twice for possible errors separately, and make certain its integrity. Pre-approved questioner regarding demographics of the patient and data collection will be used while all the testing will be done by International Organization for Standardization (ISO) certified laboratory (Shaukat Khanum Laboratory). Principal investigators will visit twice weekly the study site. Trial steering committee members will make unexpected and unplanned visits as well. There is no conflict of financial and non-financial interest with sponsors and researchers.

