### Frequency and plans for auditing trial conduct {23}

Weekly audit will be done by principal investigators. Monitors will audit by visiting trial sites while performing and resolving solutions to various problems. The monitor will verify the following variables for all patients on every visit: biodata of participants, signed informed consent, eligibility criteria, date of randomization, group allocation, treatment assigned, and adverse events if any. Auditing of the clinical trial will be done by trail steering committee in weekly zoom meeting where all the audits will be provided by the site investigators and research coordinators.

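### Paper CRFs are destroyed at data entry, before database lock, so later queries cannot be settled against them, most seriously for the daily symptom outcome

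*Protocol article*

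**What the plan says.** All references are to the protocol article.

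- **Data management {19}** makes the paper form the input to the database: "Data entry will be done electronically once paper-based case report form (CRF) has been received at the trial office". It then orders: "Once the data is entered, CRF will be destroyed to ensure safety and security". No scan, certified copy or archive is mentioned. The same section has one set of site investigators collect the data and a different set enter them.
- **Plans for assessment and collection of outcomes {18a}** describes the check at entry: "two site investigators will enter the data, recheck twice for possible errors separately, and make certain its integrity". It also says "COVID-19 symptoms evaluation will be done on daily basis" and "all the testing will be done by International Organization for Standardization (ISO) certified laboratory".
- **Data management {19}** adds a further check: "All outcomes will be double-checked by the researchers prior to data collection and data storage".
- **Who will be blinded {17a}** puts the locking of the data at the end of the trial.
- **Composition of the coordinating center and trial steering committee {5d}** assigns cleaning, editing and SAS entry as a task, whereas {18a} names Microsoft Access as the database.
- **Outcomes {12}** names three primary outcomes: "Primary outcomes will include time to SARS-CoV-2 RT-PCR clearance, alleviation of symptoms, and better high-resolution computerized tomography (HRCT) chest score". **Sample size {14}** makes the symptom time the relevant endpoint for re-estimation and the other two additional endpoints.
- **Confidentiality {27}** relies on coded participant IDs, with the linking document stored separately.

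**The concern.** A paper CRF is what a data manager returns to when a value is implausible, when two values conflict, or when a result is disputed after unblinding. Here it is destroyed at the first point in the data flow, while cleaning, editing, lock and analysis are still to come. A correction made after that point cannot be justified from the CRF, and an error found then may have to stand.

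Time to symptom alleviation is the outcome most exposed. It is built from daily assessments by site staff, and the person keying the value is not the person who saw the patient. The paper is the only named link between the two.

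**Working it through.** The plan gives no figure on this point, so there is nothing to reproduce. The check sets the sections side by side, followed by one illustrative count.

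**1. Order of events.** The CRF reaches the trial office, the data are entered, and the CRF is destroyed ({19}). Lock comes at the end of the trial ({17a}). Recruitment began on July 30, 2020 and completion was estimated for February 15, 2022 (Trial status), so forms from early patients could be gone well over a year before lock. Cleaning and editing ({5d}) have no stated position relative to destruction.

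**2. Do the planned checks come first?** The two rechecks in {18a} are described together with entry, so they may well be done while the paper exists. No section requires this. The double-check in {19} is placed before data are collected and stored, so it is not a check of the entered value.

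**3. What other record exists, by primary outcome?**

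| Primary outcome | Record outside the CRF | Retention stated? |
|---|---|---|
| RT-PCR clearance | Laboratory result ({18a}); swab samples kept at −80° ({33}) | No |
| HRCT score | The scan | No |
| Time to symptom alleviation | None named | Not applicable |

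For symptoms, a hospital chart is a possible back-up. Section {18b} says data are collected during admission (30-day mortality excepted), but it also includes home-quarantined patients. A chart therefore cannot be assumed for everyone.

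**4. Illustrative size, symptom record only.**

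- Entries per patient: 14, assuming one per day over the maximum treatment period in {11a}.
- Patients: 200 ({14}).
- Keying error rate: 0.1% to 1%. This is an assumption; the document gives none.

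Entries = 14 × 200 = 2,800.
Expected errors = 2,800 × 0.001 = 2.8, to 2,800 × 0.01 = 28, that is, about 3 to 28.

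This gives no credit for the {18a} rechecks, which would lower it. It scales with the number of days recorded, so patients who recover early contribute fewer entries. Not every error would change an outcome; those around the day of resolution matter most.

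**The case against.** The case against has real force on several points.

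- **Rechecking at entry.** The natural reading of {18a} is that data count as entered only after both rechecks. This stands as a likely mitigation, but the order is not fixed, and it does not help with queries that arise later.
- **Sources outside the CRF.** For RT-PCR and HRCT the CRF holds transcribed values, and destroying it does not destroy the laboratory report or the scan. Data coding by medical record number ({19}) also gives a route back to a chart where one exists. This stands, and it confines the main harm to symptoms.
- **Monitoring.** A reader might infer that destruction defeats the monitoring plan in {23}, which says "The monitor will verify the following variables for all patients on every visit". The list that follows contains no primary outcome, and monitors visit the sites while CRFs go to the trial office. That section does not show that checking of outcome values was planned and then made impossible.
- **Bias.** Data managers and analysts are to be blinded ({17a}), so keying errors should be mainly non-differential. No effect on type I error or direction of bias has been shown. This stands.
- **Condensed article.** Archiving details are often left to a fuller document. That would answer a complaint about silence, but here the article states a rule, and the rule is destruction at entry.

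**Conclusion.** The point holds in limited form. Paper CRFs are destroyed at data entry, ahead of lock and with no link to completed cleaning, so later queries cannot be resolved against them. This matters most for the daily symptom record. The illustrative size is about 3 to 28 keying errors in 2,800 symptom entries before rechecking, resting on 14 entries for every patient and an assumed error rate of 0.1% to 1%.

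A reader might infer more: that no primary-outcome value can ever be checked against source. The documents do not support this, because the rechecks may precede destruction and two of the three primary outcomes originate outside the CRF.

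Nor do they support a larger error count covering all three outcomes. Counting 14 symptom, 4 RT-PCR and 20 HRCT lobe entries gives 38 fields per patient, but 24 of those have a source outside the CRF. Such a count also assumes the maximum schedule for every patient, although {12} ends testing early once its criteria are met. Finally, one miskeyed RT-PCR result need not shift clearance by a 4-day interval: under the two-consecutive-negatives condition in {18b}, an isolated false negative between positives may not move it at all.

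**What to change.** Delete the destruction sentence from {19} and replace it with a retention rule. Coded CRFs, or certified copies, should be kept in locked storage through database lock, query resolution and the institution's retention period. State in {18a} that the two rechecks are made against the retained CRF.

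Because the article reports recruitment in progress, stop any destruction now and record which CRFs, if any, are already gone.

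The cost is a change of one sentence, a clarification in {18a}, and secure storage for about 200 files. Confidentiality loses nothing: coded IDs and the separately stored link in {19} and {27} already protect identity. No treatment, endpoint or analysis changes.

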### Confidentiality {27}

In addition, confidentiality of participants’ data is ensured by using participants’ IDs rather than identifiable information in the dataset (i.e., coding) and by storing the document linking the IDs to the identifiable information separately and securely.

### Plans for collection, laboratory evaluation, and storage of biological specimens for genetic or molecular analysis in this trial/future use {33}

Trained staff will collect nasopharyngeal swab samples as per biosafety and personal safety guidelines of World Health Organization. Samples will be maintained at − 80°. Patients’ follow-up will be done daily by the investigators while PCR will be repeated every 4th day for monitoring of primary end point (measuring time to return for COVID19 RT-PCR test to return negative). Patients will be evaluated clinically on daily basis; relevant investigations will be repeated as needed.

## Statistical methods

### Statistical methods for primary and secondary outcomes {20a}

Mean ± S.D will be used for quantitative data and *f*(%) will be used for categorical data. Frequency and percentages will be measured for categorical data. Data normality will be checked using the Shapiro Wilks test. If data is normal, independent sample *t*-test will be used to compare quantitative outcome such as mean hospital stay; otherwise, Mann Whitney *U* test will be used to compare median of these quantitative data. Chi-square *t*-test/ Fisher’s exact test will be applied to compare severity of symptoms and outcome (discharge or mortality), etc. For follow-up analysis, Wilcoxon test will be applied. If data supports the necessary assumptions of time to event data, survival analysis/ Kaplan Meier test will be applied. Method of analysis planned to be used in primary and secondary outcomes are mentioned in Table 1. *P* value ≤ 0.05 will be considered as significant.

**Table 1 Tab1:** Primary and secondary outcomes

Outcome	Hypothesis	Outcome measure	Method of analysis

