### Sample size {14}

Considering it a novel idea to use iodine in the management of COVID-19, no software was used to calculate the sample size (Fig. 2). However, arbitrarily 50 patients in each arm with a total of 200 patients sample size for a multi-centered study in Pakistan will be randomized. In this adaptive trial, sample size reestimation is planned to achieve the study objectives, if needed. Time taken for the elevation of the symptoms will be considered as relevant endpoint (RE) while SARS-CoV-2 RT-PCR clearance and HRCT chest score will be studied as additional endpoints (AE). The required sample size will be calculated with 0.05 alpha and 80% power of the study.

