## Assignment of interventions: allocation

### Sequence generation {16a}

Randomization will be done using lottery method. As patients might be admitted at different times so they will be recruited after taking written informed consent (following all standard protocol for infection control and disinfection) and will be randomized by selecting a slip from the box containing 50 slips of each arm labeled as A, B, C, and X. Arms A, B, and C will be the add-on interventional arms while arm X will be the placebo arm.

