**Primary outcomes**			
1. Time taken for alleviation of symptoms	Earlier symptom resolution	Yes/No	Multivariant analysis, cox proportional hazards models
2. Time taken for viral load clearance	Earlier RT-PCR negative	Positive/ negative	
3. HRCT chest score at day 4	Better score resolution	Score from 0 to 25	Mixed Ordinal Logistic Regression Model

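### Lead primary outcome is named inconsistently, and three iodine arms are judged at a flat P ≤ 0.05: chance of at least one falsely significant primary comparison about 26–33% on the inferred nine tests (13–18% favouring iodine)

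*Protocol article*

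**What the plan says.** **Outcomes.** Outcomes {12} reads "Primary outcomes will include time to SARS-CoV-2 RT-PCR clearance, alleviation of symptoms, and better high-resolution computerized tomography (HRCT) chest score". Table 1 lists the same three as primary, without ranking them. Sample size {14} says that symptom time "will be considered as relevant endpoint (RE) while SARS-CoV-2 RT-PCR clearance and HRCT chest score will be studied as additional endpoints (AE"). The section on biological specimens {33} describes time to a negative RT-PCR as the primary end point.

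**Arms.** Sequence generation {16a}: "Arms A, B, and C will be the add-on interventional arms while arm X will be the placebo arm". Trial design {8} sets 1:1:1:1 allocation and a superiority framework. Objectives {7} sets the comparison against placebo. Section {6b} says the formulations are compared to find the best route, which needs results by arm.

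**Significance.** Section {20a} gives one rule: P "value ≤ 0.05 will be considered as significant". Section {14} adds, for re-estimation, "The required sample size will be calculated with 0.05 alpha and 80% power of the study". The article gives no adjustment, no testing order, no list of contrasts and no statement of whether one or all primary outcomes must succeed. It does not state sidedness, and it makes no claim about the familywise error.

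**Method.** Section {20a} refers the reader to Table 1 for the primary and secondary outcomes. Table 1 gives "Multivariant analysis, cox proportional hazards models" for symptom time. Yet {20a} also says "If data supports the necessary assumptions of time to event data, survival analysis/ Kaplan Meier test will be applied".

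**The concern.** Three sections give three answers to which outcome leads. With three active arms and one unadjusted threshold, the text allows a claim to rest on whichever arm and outcome reaches P ≤ 0.05, and the leading outcome could be settled after the results are known. The sample size of 50 per arm is described as arbitrary, so no planned effect on a named outcome anchors the interpretation. At stake is whether a single nominally significant result is reported as evidence that iodine works. The conditional wording on survival analysis adds a smaller problem, because it makes a method already assigned in Table 1 depend on the data.

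**Working it through.** **Inputs from the article.** Three primary outcomes ({12}, Table 1); three iodine arms and one placebo arm X ({16a}); 1:1:1:1 allocation ({8}); 50 per arm ({14}); threshold 0.05 ({20a}).

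**Assumptions.** Two-sided tests. Each arm is compared with X on each outcome. The between-outcome correlation ρ is not given, so a range is shown.

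**The plan's own figure.** The only figure is the per-test 0.05. There is no stated familywise rate to reproduce. One two-sided test gives 5% in either direction and 2.5% in favour of iodine.

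**Nine tests.** Under no effect anywhere, let Z(a,j) = [X(a,j) − X(0,j)]/√2 for arm a and outcome j, with standard normal X and correlation ρ between outcomes. Sharing arm X at equal allocation gives correlation 1/(1+1) = 0.5 between arms within an outcome. Simulation (1,000,000 runs per ρ) counts trials with any |Z| > 1.960, and trials with any Z > 1.960 (iodine better):

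| ρ | Any significant | Any favouring iodine |
|---|---|---|
| 0 | 33.1% | 17.7% |
| 0.3 | 31.9% | 16.4% |
| 0.5 | 29.4% | 14.9% |
| 0.7 | 25.9% | 13.0% |
| 0.9 | 20.2% | 10.1% |

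Ignoring the shared arm, nine independent tests would give 1 − 0.95⁹ = 37.0%.

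**Other readings of the same text.**
- Symptom time only ({14}), three arms against X: 12.5% in either direction and 6.3% favouring iodine (numerical integration: 0.1254 and 0.0627).
- Pooled iodine against X, or one omnibus test per outcome (three tests): 1 − 0.95³ = 14.3% at ρ = 0, falling to about 11% at ρ = 0.7.
- One-sided tests at 0.05, nine tests: 31.5% at ρ = 0 to 22.7% at ρ = 0.7, all favouring iodine.
- Some arm must win on all three outcomes: about 0.0% at ρ = 0 to 1.2% at ρ = 0.7, favouring iodine.

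Every reading in which one significant primary comparison suffices exceeds the per-test level. Only the last falls below it, and the article does not state that rule.

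**A rule that holds 0.05.** Give each arm 0.05/3 = 0.0167 (critical value 2.394) and test the outcomes in fixed order within the arm. Under the global null an error requires the first test in some arm to reject. Integration over the shared control gives 0.0445, about 4.4–4.5%.

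**Cost.** Detectable HR = exp[2(z(1−α/2) + 0.842)/√d], where d is the number of events per pair of arms:

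| d | α = 0.05 | α = 0.0167 |
|---|---|---|
| 100 (all patients) | 1.75 | 1.91 |
| 91 | 1.80 | 1.97 |
| 83 | 1.85 | 2.03 |

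For d = 100: exp(2 × 2.802/10) = 1.75 and exp(2 × 3.236/10) = 1.91. The 83 and 91 events assume a control median of 7 days, 14 days of follow-up and HR 1.8. With exponential times, 50(1 − 0.25) + 50(1 − 0.25^1.8) = 83. With Weibull shape 1.5, day-14 survival in X is 0.141 and the sum is 91. These inputs are illustrative and are not in the article.

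**The case against.** **Deferral to an analysis plan.** Multiplicity detail is often left to a statistical analysis plan, and one may exist. This stands as far as a missing adjustment goes: absence alone would be weak. It does not dispose of the point, because the article fixes a flat threshold and contradicts itself on which outcome leads.

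**Nine tests are inferred.** No section lists contrasts, and Objectives {7} can be read as requiring all three benefits together. That is correct, so the 26–33% is conditional on the any-win reading and the alternatives are shown beside it. The inference is still reasonable given the arm-level aim in {6b} and the placebo comparison in {7}.

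**A false efficacy claim.** A reader might take 26–33% as the chance of falsely declaring iodine effective. It is not, because it counts results in either direction. With two-sided tests the chance favouring iodine is 13–18%. A range near 23–31% would apply only to one-sided testing at 0.05. Table 1 words its hypotheses directionally ("Earlier symptom resolution"), but sidedness is nowhere stated.

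**Test choice.** A reader might also infer from {20a} that the primary outcomes could be analysed by t-test or Mann-Whitney with unresolved patients dropped. The article does not support this. The example for those tests is hospital stay, the primary outcomes are sent to Table 1, no section restricts an analysis to resolved patients, and {20c} specifies intention to treat with imputation. Only the conflict between the conditional survival clause and Table 1 remains.

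**Conclusion.** The point holds in this form. Sections {12}, {14}, {33} and Table 1 disagree on the lead primary outcome, and {20a} judges every comparison at 0.05 without order or adjustment. On nine two-sided any-win comparisons, the chance of at least one falsely significant primary result is about 26–33% for ρ from 0.7 to 0, and the chance of one favouring iodine is about 13–18% against 2.5% for a single test. Symptom time alone still gives 12.5% (6.3% favouring iodine), and pooled or omnibus testing of the three outcomes gives about 11–14%. The figures rest on two-sided testing, equal arms, an assumed ρ and contrasts that the article does not list. The 5% is a per-test level, since no familywise claim is made. The contradiction and the flat threshold need no such assumption, and they should be resolved before unblinding because the trial's conclusion rests on these tests.

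**What to change.** 1. Reconcile {12}, {14}, {33} and Table 1 to one lead primary outcome before unblinding. Symptom time is the natural candidate because {14} already puts it first. The choice is the sponsor's.
2. State in {20a} the contrasts, the sidedness and a rule that holds the familywise error at 0.05. One suitable scheme is 0.05/3 for each of A, B and C against X, with a fixed order of outcomes within each arm. Other valid schemes exist.
3. Use the same alpha in the re-estimation in {14}: 0.0167 per comparison under this scheme.
4. Delete the conditional survival clause in {20a} for the primary outcomes, so that the Table 1 models apply.

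The change is one of wording. Its price is sensitivity: at 80% power the detectable HR rises from 1.75 to 1.91 if all 100 patients per pair have the event, or from about 1.80–1.85 to 1.97–2.03 with 91–83 events. Re-estimation at the smaller alpha may call for more patients.
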